Five recent RCTs assessed the possibility of extending the IVT time window to 24 h after symptom onset in patients with ischemic stroke.^[4, 5, 6, 7, 8]^ The tenecteplase reperfusion therapy in acute ischemic cerebrovascular events III (TRACE-III) trial demonstrated that in patients with confirmed anterior circulation large vessel occlusion (LVO), extended-window tenecteplase without access to MT achieved superior functional outcomes compared with standard medical care.^[4]^ However, the thrombolysis in imaging-eligible, late window patients to assess the efficacy and safety of tenecteplase (TIMELESS) trial, which also used tenecteplase in the extended time window for patients with anterior circulation LVO, most of whom underwent subsequent MT, did not show improved functional outcomes.^[5]^ Recently, the treatment with intravenous alteplase in ischemic stroke patients with onset time between 4.5 and 24 hours (HOPE) trial evaluated IVT with alteplase in patients with salvageable brain tissue within 4.5 to 24 h, showing functional benefit.^[6]^ The Chinese Acute Tissue-Based Imaging Selection for Lysis in Stroke-Tenecteplase II (CHABLIS-T II) trial revealed that tenecteplase increased reperfusion without symptomatic intracranial hemorrhage in patients selected by imaging in late-time window treatment.^[7]^ The Extending the Time Window for Thrombolysis in Posterior Circulation Stroke without Early computed tomography (CT) Signs (EXPECTS) trial demonstrated that in patients with predominantly mild posterior circulation stroke who did not undergo mechanical thrombectomy (MT), IVT administered 4.5 to 24 h after onset led to superior functional outcomes compared with standard medical care.^[8]^

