### Randomization and blinding

Patients are randomized, in a 1 : 1 ratio, using a minimization process to receive either intravenous tenecteplase or standard medical treatment, stratified by vessel occlusion location (anterior or posterior circulation), age (<65 or ≥65 years), baseline NIHSS (<16 or ≥16) and center. The randomization will be done by a computerized central interactive web response system. All endpoints will be evaluated by an independent investigator who is unaware of the treatment group.

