### Safety outcomes

The safety outcomes are (1): Proportion of patients with sICH within 36 h, as defined by Heidelberg bleeding classification;^[26]^ (2): Proportion of systemic bleeding within 90 (±7) days, as defined by The Global Utilization of Streptokinase and Tissue Plasminogen Activator for Occluded Coronary Arteries (GUSTO): moderate and severe bleeding; (3): Mortality within 90 (±7) days.

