### Sample size estimation

The sample size is based on the primary outcome. Based on the reported pooled data of the stroke thrombolysis trials in the extended time window,^[27]^ we expect a 12% absolute difference in the proportion of patients reaching the primary outcome between patients treated with tenecteplase and standard medical treatment (expected rate of excellent functional outcome 50% in patients treated with tenecteplase and 38% in patients treated with standard medical treatment). Considering the potential impact of one interim efficacy analysis on the probability of type I error, we adjusted the alpha error to a two-sided alpha of 0.049. The total sample size of 568 (*n* = 284 per treatment group) will have 80% power to detect the specified difference at the two-sided 0.049 significance level, with a 5% dropout rate.

One efficacy interim analysis is planned when 50% of the target sample size has completed 90-day follow-up. A Lan-DeMets alpha spending function will be used to control the overall alpha level, using O’Brien and Fleming boundaries (corresponding to an alpha level of 0.003 and 0.049 at the interim and final analysis, respectively).

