### Statistical analysis

The analysis population for the efficacy analyses will be performed on the intention-to-treat (ITT) population. For the primary outcome, the proportions of mRS 0-1 at 90 (±7) days will be compared between two treatment groups using a modified Poisson regression. The risk ratio (RR) and its 95% confidence interval (CI) will be reported. We will also perform adjusted analysis of the primary outcome with adjustment for pre-specified covariates.

The distribution of mRS score at 90 (±7) days will be analyzed using ordinal logistic regression, with treatment effect reported as a common odds ratio and its corresponding 95% CI. If the proportional odds hypothesis is rejected, the generalized odds ratio (GenOR) with 95% CI will be calculated. For binary secondary efficacy endpoints, modified Poisson regression model will be employed to determine RR and its 95% CI. For continuous secondary efficacy endpoints, linear regression models will be employed to estimate mean difference as a measurement of treatment effect. In case the normality assumption for the residuals is violated, win ratio will be calculated. Safety analyses will be performed on the safety population who received one of the study interventions according to the treatment they actually received. Safety endpoints will be compared using the modified Poisson regression. Subgroup analyses include age (<65 years and ≥ 65 years), time from symptom onset (last-seen-well) to randomization (>4.5-9 h and >9-24 h and stroke on awakening), baseline NIHSS score (<10 and ≥10), vessel occlusion location (anterior circulation and posterior circulation), occlusion site (M2 segment of MCA, M3-M4 segment of MCA, ACA, PCA and stenosis), baseline serum glucose (<100 mg/dL and ≥100 mg/dL) and baseline systolic blood pressure (≤140 mmHg and >140 mmHg).

Three safety interim analyses were planned when the first 100, 200, 300 patients have completed the 90-day follow-up. One efficacy interim analysis was planned to be conducted when 50% of the total patients have completed the 90-day follow-up. All statistical analyses will be performed following a statistical analysis plan (SAP) which will be finalised before the database lock and unblinding of the trial. SAS software version 9.4 (SAS Institute) and R version 4.4.1 will be used for the statistical analyses.

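### Modified Poisson regression, fixed for all safety endpoints, gives a spurious risk ratio and p-value if one arm has no sICH or no moderate/severe bleeding

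*Protocol article*

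**What the plan says.** The Statistical analysis section of the protocol article gives one rule for harms: "Safety endpoints will be compared using the modified Poisson regression". The Safety outcomes section lists three endpoints, all binary: "Proportion of patients with sICH within 36 h, as defined by Heidelberg bleeding classification"; "Proportion of systemic bleeding within 90 (±7) days", limited to GUSTO moderate and severe events; and "Mortality within 90 (±7) days".

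The analysis set is as treated: "Safety analyses will be performed on the safety population who received one of the study interventions according to the treatment they actually received". Arm size follows from the Sample size estimation section, "The total sample size of 568 (*n* = 284 per treatment group) will have 80% power".

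The Statistical analysis section does give fallbacks for other models: a generalized odds ratio if proportional odds fails, and a win ratio if residuals are not normal. It gives none for the safety model. It names SAS 9.4 and R 4.4.1 as software. It also says that an SAP will be finalised before database lock and unblinding; that SAP is not available here. No expected rate of sICH or systemic bleeding appears anywhere in the article.

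**The concern.** Modified Poisson regression is a Poisson model with log link and a robust (sandwich) variance. It is a sound default for a risk ratio when both arms have events. With no events in one arm, the log risk ratio runs off to infinity and the iteration stops at an arbitrary large value. A model-based variance would at least signal this by becoming huge. The sandwich variance does not: it is built from squared residuals, and in the empty arm these are close to zero.

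Two of the three safety endpoints may be rare, and under the Intervention section the control arm receives a single antiplatelet agent and no thrombolytic, so an empty control cell is plausible. sICH is the main harm to set against any benefit of tenecteplase. A meaningless p-value there, or a change of method after the counts are known, would weaken the benefit-risk conclusion.

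**Working it through.** **Inputs.** From the article: 284 patients per arm, binary endpoints, modified Poisson regression. Assumed, because the article gives none: the event rates. Slightly smaller as-treated arms would change little: with 270 per arm, the chance of an empty arm is 26% at a 0.5% rate and 6.6% at 1%.

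**The plan's own figure.** For 50% vs 38%, two-sided alpha 0.049 and 80% power, the pooled-variance formula without continuity correction gives 270 per arm. Then 270 × 1.05 = 283.5, rounded up to 284, or 568 in total. The stated sample size is reproduced.

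**Variance with an empty arm.** With events in both arms (x1 and x0, each of n), the robust variance of the log risk ratio is (1/x1 − 1/n) + (1/x0 − 1/n). When x0 = 0, the fitted control rate is driven to nearly zero and the control arm contributes about 0. The standard error becomes sqrt(1/x1 − 1/284):

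- x1 = 1: sqrt(1 − 0.0035) = 0.998
- x1 = 3: sqrt(0.3333 − 0.0035) = 0.574
- x1 = 8: sqrt(0.125 − 0.0035) = 0.349

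**Fits at 284 per arm** (Python statsmodels, HC0; each flagged as converged):

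| Events | RR | Robust SE | p | Fisher p |
|---|---|---|---|---|
| 1 vs 0 | 7×10^8 | 0.998 | 10^-92 | 1.00 |
| 3 vs 0 | 2×10^9 | 0.574 | 10^-303 | 0.25 |
| 5 vs 0 | 2×10^9 | 0.443 | 10^-507 | 0.061 |

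R shows the same failure. For 1 vs 0 it gives a risk ratio of 4.6×10^7, 95% CI 6.6×10^6 to 3.3×10^8, p about 5×10^-70. The ratio differs between packages because it depends on where the iteration stops. HC3 does not help (SE 1.002 for 1 vs 0). The model-based SE in R is 1,500 to 4,100 (p about 0.99), so the fault lies in the robust variance. SAS was not tested.

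**Where a valid test agrees.** Fisher's p is 0.030 at 6 vs 0 and 0.007 at 8 vs 0. From 6 vs 0 upward the direction is supported and only the size of the ratio and its finite upper limit are spurious.

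**Events in both arms** (robust Wald p, then Fisher p): 8 vs 1, 0.049 and 0.038; 5 vs 2, 0.27 and 0.45; 10 vs 2, 0.037 and 0.037; 12 vs 2, 0.018 and 0.012. There is no breakdown.

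**Chance of an empty arm**, q = (1 − p)^284:

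| Assumed rate | 0.25% | 0.5% | 0.75% | 1% | 1.5% | 2% |
|---|---|---|---|---|---|---|
| q | 49% | 24% | 12% | 6% | 1.4% | 0.3% |

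**Type I error with equal true rates.** Every table with exactly one empty arm rejects, which has probability 2q(1 − q).

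- At 0.5%: 2 × 0.2409 × 0.7591 = 0.366. Tables with events in both arms add almost nothing, so the total is 37%.
- At 1%: 2 × 0.0576 × 0.9424 = 0.109. The other tables add 0.003, so the total is 11%.
- At 2%: 2 × 0.0032 × 0.9968 = 0.006. The other tables add 0.023, so the total is 3%, below nominal.

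Fisher's test stays below 2.5% at each of these rates.

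**The case against.** The best reply is that zero-cell handling belongs in the SAP, which a condensed article need not reproduce. That stands in part: the SAP may hold such a rule, and a reader should not infer from the article that the trial has none. The point is narrower. The article commits to a method for every safety endpoint without qualification, and that method gives a wrong answer in a plausible case.

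A second reply is that the chance of harm is smaller than the chance of an empty control arm suggests. A misleading significance call also needs 1 to 5 events on tenecteplase. At an assumed 3% tenecteplase rate, that joint probability is 7.1, 3.5, 1.7 and 0.8% for control rates of 0.25, 0.5, 0.75 and 1%. It is 21% if the rates are 1% and 0.5%. This stands.

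A third is that a ratio near 10^8 beside counts of 1 and 0 would be noticed, and that independent committees review safety. That makes silent publication unlikely. It does not settle which analysis replaces the failed one once the data are known.

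Two stronger readings are tempting. One is that the interval is also unreliable with one or two events in an arm; the comparisons above do not bear this out. The other is that the Introduction's remark on an earlier trial, "tenecteplase increased reperfusion without symptomatic intracranial hemorrhage", predicts an empty arm here. It concerns tenecteplase in another study and says nothing about this control arm.

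**Conclusion.** The concern holds for a zero cell and no further. If either arm has no sICH or no GUSTO moderate or severe bleeding, the stated analysis yields an invalid ratio, interval and p-value. With 1 to 5 events against 0 it also declares a difference that Fisher's test does not.

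How likely this is rests on assumed rates: material at about 1% or below, and unlikely at 1.5 to 2% or above. Mortality is unlikely to be affected. The documents do not support abandoning modified Poisson regression when both arms have events, nor a minimum event count for using it on mortality. Severity is minor to moderate; the primary efficacy analysis and the sample size are untouched.

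**What to change.** Before unblinding, add a sentence to the SAP, and qualify the article's rule to match. For sICH and GUSTO moderate or severe bleeding, if either arm has no events, the comparison will be a risk difference with a score-based (Miettinen-Nurminen) 95% confidence interval and an exact p-value, in place of the modified Poisson risk ratio. These may also be reported beside the risk ratio in all cases.

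Valid intervals remain readable in the sparse case. The Newcombe risk-difference interval, for illustration, is −1.0% to 2.0% at 1 vs 0 and −0.4% to 3.1% at 3 vs 0. The sentence should also say whether the interval or the p-value leads, since they can disagree: at 5 vs 0 the Newcombe interval is 0.1% to 4.1% while Fisher's p is 0.061.

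The cost is wording only. The small downside is that two effect measures may appear in the safety table.

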### Data safety and monitoring board

An independent data safety and monitoring board (DSMB) will regularly monitor the safety of the trial and guarantee the safety of all patients. The DSMB will perform safety reviews when the first 100, 200 and 300 patients are enrolled and complete 90-day follow-up. If there are concerns about safety, the DSMB will make a recommendation to the trial steering committee about continuing, stopping or modifying the trial. One prespecified efficacy interim analysis will be performed when 284 patients have completed 90-day follow-up. Results of the interim analysis will only be presented to the DSMB.

Due to the fast speed of enrollment, after review with the DSMB in June 2025, the original interim analysis plan was considered no longer to serve its purpose. On the recommendation of the DSMB, the steering committee rescinded the planned efficacy interim analysis and the third safety analysis. Since no formal assessment of efficacy is done and no alpha is spent, we will not adjust the alpha level or p values for the final analysis.

### Study organization and funding

OPTION is an investigator initiated clinical trial. It is sponsored by Yangfan 3.0 Diagnosis and Treatment Capability Enhancement Project (ZLRK202514) and CSPC Recomgen Pharmaceutical (Guangzhou) Co., LTD (Guangzhou, China). The funders have no role in the design, conduct, statistical analysis or reporting of the results. A steering committee provides scientific and strategic guidance for the trial. An executive committee manages the day-to-day activities of the trial. Endpoint events, safety endpoints and SAEs are reviewed by a CEC and all clinical imaging data are independently reviewed by an imaging core laboratory.

## Discussion

The OPTION trial is a pivotal study designed to evaluate the efficacy and safety of intravenous tenecteplase in patients with AIS presenting within 4.5-24 h from symptom onset, who have a non-LVO and demonstrate salvageable tissue on perfusion imaging. However, unlike the conspicuous identification of LVO, accurate localization of the occlusion site in non-LVO often poses a diagnostic challenge. We utilize a pragmatic imaging selection approach, enrolling patients who demonstrate salvageable penumbral tissue after exclusion of LVO. The advantages of this imaging selection are that it can exclude patients with clear indications for MT, and also enhance detection rates of distal and posterior circulation vessel occlusions by combining CTA with CTP.^[28,29]^ Another ongoing randomized trial evaluating tenecteplase in patients with non-LVO treated in the extended time window is Randomization to Extend Stroke Intravenous ThromboLysis In Evolving Non-Large Vessel Occlusion With TNK (RESILIENT EXTEND-IV, NCT05199662). The databases will be pooled after both trials are completed and published.

## Conclusions

The OPTION trial will provide evidence regarding the efficacy and safety of tenecteplase 4.5 to 24 h in patients with AIS due to non-LVO.
